### Study design

The CASP intervention will be tested in the form of a 1:1 non-randomized, controlled pilot study. The pilot study will consist of two arms, comparing the CASP intervention in the two districts of Balod and Rajnandgaon against Enhanced Usual Care in the two districts of Mungeli and Balodabazar.

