### Sample size

Since the present study is a pilot study (focused primarily on understanding feasibility and refining processes in anticipation of a full-scale trial), the sample size calculation is based on a conservative assumed rate of the secondary outcome (change in suicide attempts) of 10% at the end of 12 months in the control group. Thus, a minimum enrolment of 500 participants (250 control; 250 intervention) has a power of 80% (at a 2-sided alpha level of 0.05) to detect an absolute risk reduction of 10 percent points (minimal detectable difference of 10% between the groups (intervention and control), while allowing for an expected 20% loss to follow-up over the 12 months follow-up period.

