### Data analysis

*Implementation outcomes*

Descriptive statistics (means, medians and standard deviations) of the reach, adoption and implementation metrics will be calculated. Qualitative thematic analysis
^
27
^ of the in-depth interviews exploring feasibility and acceptability will be carried out using a mix of inductive and deductive approaches. Two coders will independently review transcripts, generate initial codes, and collaboratively develop a comprehensive codebook (initial coding). This will be followed by a pilot coding phase to ensure procedural consistency before independent coding of the remaining transcripts, with discrepancies resolved through consensus or third-rater consultation. Researchers will then interpret and refine final themes. Coding will be done using NVivo 1.4.1.

*Clinical outcomes*
1.Difference in percentage of re-attempted suicide and death by suicide

We will analyze the difference between the intervention and control group in the percentage of participants who, after initial visit in the hospital for a suicide attempt, have re-attempted suicide (including deaths by suicide) at 6 and 12 months of follow-up. For statistical analysis, we will use Bayesian binominal testing as implemented in the open software program JASP.
^
28
^ Bayesian analysis allows us to not only test whether the null hypothesis is true or false, but also to test how likely the alternative hypothesis (that the change in suicide rates between intervention and control) is given the data.
^
29,
30
^
2.Change in depression, suicide risk and TiC-P scores

The mean change in depression and suicidal behavior scores between baseline and 6-
and 12-
months follow-up within the intervention group will be calculated using Bayesian linear mixed models as implemented in JASP. Models will be estimated both with and without a random effect for location, to see if it is needed to control for any clustering effect.
^
31
^
3.Quality of life

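### The stated 80% power treats participants as independent, although the arm is set by whole district with two districts per arm

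*Protocol article*

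**What the plan says.** All references are to the protocol article.

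- **Sample size.** The calculation uses a "conservative assumed rate of the secondary outcome (change in suicide attempts) of 10% at the end of 12 months in the control group". It concludes that "a minimum enrolment of 500 participants (250 control; 250 intervention" in total "has a power of 80% (at a 2-sided alpha level of 0.05) to detect an absolute risk reduction of 10 percent points", while "allowing for an expected 20% loss to follow-up over the 12 months follow-up period". No ICC, design effect or number of clusters is given.
- **Study design.** The study is a "1:1 non-randomized, controlled pilot study", "comparing the CASP intervention in the two districts of Balod and Rajnandgaon against Enhanced Usual Care in the two districts of Mungeli and Balodabazar". A participant's arm follows from the district.
- **Data analysis, Clinical outcomes, item 1.** For the between-arm comparison of re-attempts: "For statistical analysis, we will use Bayesian binominal testing as implemented in the open software program JASP". No district term is stated.
- **Data analysis, Clinical outcomes, item 2.** For the depression and suicidal-behaviour scores within the intervention group: "Models will be estimated both with and without a random effect for location, to see if it is needed to control for any clustering effect". This is the only mention of clustering.
- **Aims, Outcomes and Progression criteria.** Re-attempt is a secondary outcome, and none of the progression criteria in Table 2 concerns it.

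**The concern.** When whole districts define the arms, people in the same district share services, supervision and population, and their outcomes may be correlated. The arm difference then carries between-district variation that adding people within a district does not average out. With two districts per arm and many participants in each, even a small ICC matters.

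The article states a frequentist power at a two-sided 5% level. If that figure assumes independence, a null re-attempt result could be read as coming from a study with an 80% chance of finding a 10-point difference, when the chance may have been much lower. The question is whether the 250 per arm already contains an allowance for this.

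**Working it through.** **Inputs from the Sample size section:** two-sided alpha 0.05, power 80%, 10-point difference, 250 enrolled per arm, 20% loss. Evaluable per arm: 250 × 0.8 = 200.

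**Step 1. Reproduce the stated figure.** The usual two-proportion formula is

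n per arm = [1.96·√(2·p̄·(1−p̄)) + 0.8416·√(p1(1−p1) + p2(1−p2))]² / (p1−p2)², where p̄ is the mean of p1 and p2.

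- *Literal rates, 10% v 0%:* p̄ = 0.05; (0.6041 + 0.2525)²/0.01 = 73.4, so 74 per arm. Power at 200 per arm is 99.7%. The stated 80% is not reproduced.
- *20% v 10%:* p̄ = 0.15; (0.9897 + 0.4208)²/0.01 = 198.96, so 199 per arm. With the loss allowance, 199/0.8 = 249, against 250 stated. Power at 200 per arm is 80.2%. Size and power are both reproduced.

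The allowance for loss takes the calculation from 199 to 249. Nothing remains in the 250 that could be an allowance for clustering.

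**Step 2. Add clustering.** Two assumptions are needed, because the article supplies neither figure:

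- 100 evaluable per district (an equal split of 200 over two districts);
- an ICC between 0 and 0.05.

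Design effect = 1 + (100 − 1)·ICC. Effective n per arm = 200 / design effect. Power = Φ{[|p1−p2|·√n − 1.96·√(2·p̄·(1−p̄))] / √(p1(1−p1) + p2(1−p2))}.

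Example at ICC 0.01: design effect 1.99, effective n 200/1.99 = 100.5. For 20% v 10%, [0.1·√100.5 − 0.9897]/0.5 = 0.026, and Φ(0.026) = 51%.

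| ICC | Design effect | Effective n per arm | Power, 20% v 10% | Power, 10% v 0% |
|---|---|---|---|---|
| 0 | 1.00 | 200 | 80% | 99.7% |
| 0.001 | 1.10 | 182 | 76% | 99% |
| 0.005 | 1.50 | 134 | 63% | 97% |
| 0.01 | 1.99 | 101 | 51% | 91% |
| 0.02 | 2.98 | 67 | 37% | 76% |
| 0.05 | 5.95 | 34 | 21% | 47% |

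On 10% v 0%, power crosses 80% at an ICC of about 0.017.

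**Step 3. Can enrolment make up the loss?** With two districts per arm, effective n per arm approaches 2/ICC however many people are enrolled. At ICC 0.01 that ceiling is 200, and 199 is needed for 20% v 10%. From about that ICC upward, no realistic enrolment in these four districts restores 80%.

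**Step 4. What if the test ignores district?** The table assumes a test that holds its 5% level. In a beta-binomial simulation of 20% v 10%, an unadjusted test rejects more often than the table shows (77% at ICC 0.005, 74% at 0.01). Its true two-sided type I error is then about 11% and 16%, so the claim of 80% power at alpha 0.05 is not met that way either.

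**The case against.** **The headline series uses a rate that the article does not state.** The article gives 10% in the control group and never mentions 20%. A reader might infer that 80% is overstated whichever rates are used. The documents do not support that: on the literal 10% v 0%, the design effect alone leaves power above 80% up to an ICC of about 0.017. The literal rates do not produce the stated 80%, however, and the only pair found to give both the size and the power is 20% v 10%. This objection stands as a condition on the finding.

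**The size of the loss is unknown.** No ICC is given, and the range runs from a trivial loss to a severe one. It cannot be said outright that the study lacks 80% power, since at ICC 0 the figure holds. The equal split is also assumed. District populations differ (about 1.8 and 0.8 million in the intervention arm, 1.31 and 0.70 million in the control arm), and unequal enrolment would lower power further.

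**The random effect for location may be over-read.** It might be taken as acceptance that district clusters re-attempts. It applies only to score models within the intervention group, and location is not defined as district. It shows general awareness of clustering and no more.

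**A harsher figure is available.** A t-test on four district rates (2 degrees of freedom) has about 36% power for 20% v 10% even at ICC 0. That should not be presented as this study's power: the article plans no such test, and the low figure comes largely from the test's critical value.

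**The consequence is modest.** Re-attempt is secondary, the study is a pilot, and no progression criterion uses the comparison. A reader might also infer that this calculation will size the definitive trial. The article does not say so; it foresees a randomised trial, which is a different design.

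**It could be left to the analysis plan.** Details of the model could. A published power figure that rests on an unstated independence assumption can be corrected where it stands.

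**Conclusion.** The point holds in a conditional form. The 80% is the power of an independent-individual comparison at 20% v 10%, with an allowance for loss and none for clustering, in a design that sets the arm by district with two districts per arm. On that reading any positive ICC lowers it: to 76% at 0.001, 51% at 0.01 and 21% at 0.05. These values rest on an assumed ICC range, an assumed 100 evaluable per district and a normal approximation.

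The fault is separate from the inconsistent event rates. Restating the rates as 20% v 10% would repair the arithmetic and leave the clustering gap. Because the loss is not determined by the documents, and the outcome is secondary and gates nothing, this calls for a correction of the stated figure and not a redesign.

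An ICC range does not cover one further limit. The districts are few and not randomised. The Control condition section describes an active, staffed mental health programme with monthly awareness camps in the control districts, and no existing suicide follow-up and no such camps in the intervention districts. District differences of this kind are confounded with the intervention effect.

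**What to change.** In the Sample size section, together with the correction of the event rates:

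1. State that the 80% holds only if outcomes are independent within district.
2. Give the power over a stated, assumed ICC range (for example 0.001 to 0.05), with the assumed evaluable number per district.
3. Describe the between-arm re-attempt comparison as estimation with an interval, not as a powered test.
4. State that four non-randomised districts cannot separate district differences from the intervention effect.
5. Do not use a district ICC from this pilot as the basis for sizing the definitive trial. Four districts leave 2 degrees of freedom between districts within arms, so the estimate would be too imprecise, and it would be mixed with differences in existing services.

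The cost is a few sentences and a less favourable stated power. Enrolment and study procedures do not change, so this can be done while recruitment and follow-up continue.

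### The sample-size inputs do not fit together: a 10-point absolute reduction from a 10% control rate means 0% under CASP, and 250 per arm at 80% power does not follow from that

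*Protocol article*

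**What the plan says.** All the inputs stand in one paragraph of the Protocol article, Sample size.

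- Control rate: a "conservative assumed rate of the secondary outcome (change in suicide attempts) of 10% at the end of 12 months in the control group".
- Error rates and effect: the design "has a power of 80% (at a 2-sided alpha level of 0.05) to detect an absolute risk reduction of 10 percent points", with the effect restated as a "minimal detectable difference of 10% between the groups (intervention and control").
- Size: "a minimum enrolment of 500 participants (250 control; 250 intervention"), with 20% expected loss over 12 months.

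No intervention-arm rate is given, and no other section gives a different control rate or effect. Study design describes a "1:1 non-randomized, controlled pilot study", "comparing the CASP intervention in the two districts of Balod and Rajnandgaon against Enhanced Usual Care in the two districts of Mungeli and Balodabazar". The Aims section lists the between-arm difference in re-attempt as a secondary aim.

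**The concern.** The control rate and the absolute reduction together fix the intervention rate at 0%. Nobody would plan on eliminating re-attempts in people who have just made an attempt, and a contrast that extreme needs far fewer than 250 per arm. At least one of the four stated quantities (control rate, effect, power, n) must therefore be wrong or mislabelled.

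What is at stake is how the between-arm re-attempt result will be read. It is the only clinical outcome the plan compares between arms, and it is the stated basis for enrolling 500 people. A reader who takes the paragraph at face value cannot tell which effects the study could detect. If the control rate is 10%, a halving of re-attempts would be found only about half the time, and an inconclusive result could be mistaken for evidence of no effect.

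**Working it through.** **Inputs** (all from Sample size): control rate p1 = 0.10; absolute reduction 0.10; two-sided alpha 0.05 (z = 1.960); power 80% (z = 0.8416); 250 enrolled per arm; 20% loss, so 250 × 0.8 = 200 evaluable per arm.

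**Formula** (two proportions, pooled variance under the null), with d = p1 − p2 and p̄ = (p1 + p2)/2:

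n per arm = [1.960·√(2p̄(1−p̄)) + 0.8416·√(p1(1−p1) + p2(1−p2))]² / d²

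power = Φ{ [d√n − 1.960·√(2p̄(1−p̄))] / √(p1(1−p1) + p2(1−p2)) }

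Enrolled = n / (1 − 0.20).

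**Step 1. The plan's figure from its own inputs, 10% v 0%.**
- p2 = 0.10 − 0.10 = 0; p̄ = 0.05.
- n = [1.960·√0.095 + 0.8416·√0.09]² / 0.01 = (0.604 + 0.252)² / 0.01 ≈ 73.4, so 74. Enrolled: 74/0.8 = 92.5, so 93.
- Power at 200 per arm: (0.10·√200 − 0.604)/0.300 = (1.414 − 0.604)/0.300 = 2.70, so 99.7%.

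The stated 250 is not reproduced. Other methods do not rescue it:

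| Method, 10% v 0% | Evaluable per arm | Enrolled per arm |
|---|---|---|
| Pooled | 74 | 93 |
| Continuity-corrected | 93 | 117 |
| Unpooled | 71 | 89 |
| Arcsine | 38 | 48 |
| Fisher's exact (82.3% power at 80) | about 80 | about 100 |

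**Step 2. Could 10% be a relative reduction?** The text says absolute and percentage points. The numbers also rule it out: 10% v 9% needs 13,495 evaluable per arm.

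**Step 3. Which rates give 250?** Keep the 10-point difference and try 20% v 10%.
- p̄ = 0.15; n = [1.960·√0.255 + 0.8416·√0.25]² / 0.01 = (0.990 + 0.421)² / 0.01 ≈ 198.97, so 199. Enrolled: 199/0.8 = 248.75, so 249 per arm (498 in all).
- Power at 200 per arm: (1.414 − 0.990)/0.500 = 0.849, so 80.2%.

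This matches the stated n, power, loss and 10-point difference. Solving the other way, 200 per arm give 80% power for a 10-point reduction when the control rate is about 20.1%. The pair 10% v 3% also comes near (194 evaluable, 243 enrolled), but it is a 7-point difference and contradicts the stated 10.

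**Step 4. What 200 evaluable per arm can detect if the control rate is 10%.**
- Solving power = 80% gives p2 = 3.1%: a difference of 6.9 points, and 6.9/10 = 69% relative reduction.
- 10% v 5%: (0.05·√200 − 1.960·√0.13875)/√0.1375 = (0.707 − 0.730)/0.371 = −0.062, so power is 47.5%. That contrast would need 435 evaluable (435/0.8 = 543.75, so 544 enrolled) per arm.

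All these figures treat participants as independent.

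**The case against.** Several points on the other side are fair.

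- **Zero is a boundary value, not a logical impossibility.** A reader might call the statement arithmetically impossible. A 0% rate is implausible as a target; what fails is the fit between rate, effect, n and power. This stands.
- **The 20% rate is nowhere in the document.** A reader might infer that the study was really sized for 20% versus 10%. The match is close, but it is an inference. The paragraph also labels its 10% as the rate of a change in attempts, mixing a rate with a difference, so a slip of wording is a live explanation. Only the sponsor can say which rates were used. This stands.
- **The error does not run in one direction.** With a 10% control rate, the detectable absolute difference is 6.9 points, smaller than the 10 claimed. It would be wrong to say that correction only makes the figure less favourable. Nor does the protocol claim power for 10% versus 5%; that figure is given for interpretation only.
- **The outcome is secondary in a pilot.** A reader might infer that the definitive trial would be planned from this figure. The Progression criteria section rests on recruitment, retention of participants and CHOs, and qualitative feasibility and acceptability. It uses neither re-attempt nor the power claim.
- **Clustering and the Bayesian analysis.** It is tempting to put a number on the power lost to district allocation, or on the chance of a convincing Bayes factor. The document gives no intraclass correlation, prior or Bayes-factor threshold, so any such number would rest on outside assumptions. With two districts per arm it would also depend heavily on the method chosen.

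None of this reconciles the four stated quantities.

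**Conclusion.** The sample-size statement is internally inconsistent and needs correction. On its own inputs the contrast is 10% versus 0%, which needs 74 rather than 200 evaluable per arm and has 99.7% rather than 80% power at 200; ten points is not the minimal detectable difference at a 10% control rate. The most likely explanation is a 20% versus 10% calculation with the 10% assigned to the wrong arm, but that is unproven.

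The recomputed figures rest on a two-sided 5% two-proportion test, exactly 20% loss in each arm, and independent participants. Because arm is allocated by district, with two districts per arm, any positive within-district correlation would lower power, so the power figures are upper bounds.

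The consequence is confined to the secondary between-arm re-attempt comparison and the stated reason for enrolling 500. The primary implementation outcomes and the progression criteria are unaffected.

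**What to change.** Keep n = 500 and rewrite the Sample size paragraph.

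1. State the re-attempt rates actually assumed in both arms, and call the 10% a rate rather than a change. The rates should be those used in the calculation, not chosen now because they return 250.
2. If the control rate was 20% and the intervention rate 10%, say so and give the basis for 20%; the 80% power and 10-point difference then stand.
3. If the control rate is 10%, replace the power statement: 200 evaluable per arm have 80% power for 10% versus 3.1% (6.9 points, a 69% relative reduction) and about 48% for 10% versus 5%.
4. Either way, add a sentence that the figures assume independent participants although arm is assigned by district, two per arm, and so are upper bounds on power.

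The cost is one paragraph of text, with no extra participants and no change to design or data collection. It should be settled before the re-attempt results are interpreted; Study status says that recruitment and follow-up are still under way.

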### Training

All emergency nurses and Community Health Officers (CHOs) in the selected districts will be required to undergo CASP training, organized by the state government. The training sessions will be conducted by Master Trainers, a cadre of Rural Medical Assistants (RMAs) who will first receive a three-day training led by the study’s Principal Investigators ([name]). RMAs, trained under the Chhattisgarh RMA scheme, are formally qualified medical personnel working across Health and Wellness Centres in the state.

CHOs will participate in a two-day training program covering key topics such as understanding suicide and associated risk factors, empathetic communication, safety planning, suicide risk assessment, contact procedures, data recording, privacy and confidentiality, emergency response protocols, and self-care strategies to mitigate burnout.

Emergency nurses from all Primary Health Centres (PHCs), Community Health Centres (CHCs), and District Hospitals will undergo a one-day training delivered by Master Trainers. This training will focus on understanding suicide and its risk factors, empathetic communication, and obtaining verbal consent for study participation.

Additionally, a one-day refresher training will be provided to all health workers six months after the initial training to reinforce key concepts. Training materials will also be made available to health workers throughout the study to support their ongoing learning and implementation of CASP protocols.

### Supervision

In-person supervision will occur once a month in the districts and will be carried out by the research team. At supervision meetings, CHOs who are conducting follow-ups and nurses at the hospitals will be invited to meet with the research team and discuss challenges in implementation and carrying out of project tasks. Implementation of the project activities will be supported by the Master Trainers who are based in health facilities in the chosen districts, as well as by the District Coordinators who oversee CHOs in the districts.

### Outcomes

As this is a pilot study, the primary outcomes of interest are related to its implementation, specifically: reach, adoption, implementation (including cost), feasibility and acceptability, as summarized in
Table 1. The RE-AIM framework will serve as the guiding conceptual framework for the primary outcomes in this study.
^
20,
21
^ Secondary outcomes include suicidal behaviour (including intention, ideation, planning and fatal or non-fatal suicide attempt) and symptoms of depression over a 6-
and 12-month follow-up period.

**Table 1. T1:** Implementation outcomes, indicators and timepoints of data collection.

Outcome	Indicator	Data source	Data collection
**Reach**	1) Absolute number and proportion of people who agreed to join the study	Study data (Nurses records)	Process data (during study period)
	2) Participant attrition/retention rate at endline (5 sessions)	Study data (CHOs records)	
	3) Demographic characteristics of participants compared to non-participants (Refusals and Lost to Follow up cases ^1^)	Study records	
**Adoption**	Nurses: Number and % of health centres where participants were identified and recruited	Study records	Process data (during study period)
	CHOs: Number and % of trained CHOs who deliver the CASP intervention		
**Implementation**	Of intervention: Proportion of CASP sessions which were delivered as per CASP intervention delivery schedule (on time)	CHO records	Process data (during study period)
	Of training: Change in knowledge, attitudes and skills of delivery agents (CHOs)	Pre-post survey of knowledge, skills and attitudes	Pre-pilot and at 18 months (sustained impact)
	Intervention costs, costs of (healthcare) resource use and quality of life	TiC-P and EQ-5D-5L with random sub-sample of 50 participants per condition (n=100)	Baseline and 6 months follow up
**Feasibility**	Extent to which health workers felt CASP is feasible to deliver	Semi-structured interviews with a purposive sample of health workers (n=20)	After concluding participant recruitment
**Acceptability**	Extent to which participants felt CASP is acceptable	In-depth interviews with a random sample of n=20 participants per district (total n=40)	After final contact point

^1^
Lost to Follow Up refers to individuals who have provided verbal consent to nurses in emergency wards, but with whom we have not been able to make subsequent contact and so therefore have not been formally recruited into the study.

*Primary outcome measures*

A brief survey collecting data on age, gender, education, marital status, employment status, caste/tribal background and income will be used to collect participant demographic information.

**Reach** will be measured by the absolute number, proportion, and representativeness of individuals who participate in CASP and how representative participants are compared to the target population.
**Adoption** will be measured by the absolute number and proportion of health facilities and intervention agents who are willing to initiate and carry out CASP.

**Feasibility** will be measured using semi-structured interviews exploring the perceptions of health workers and supervisors on the extent to which CASP is viable as a suicide prevention response within the health system. Within these interviews, we will also explore the feasibility of health system adoption beyond the study, e.g. what supervision pathways can be established for maintenance and scale-up of the programme (as during the pilot, supervision will be carried out by the research team).

**Acceptability** of intervention delivery will be measured qualitatively via the same interviews with health workers and supervisors specifically to assess comfort with the CASP training and intervention content. Acceptability for participants will be measured qualitatively via in-depth interviews with a random sample of n=20 participants per district (total n=40) after their last session of CASP which will explore participant comfort with CASP session content and structure and to solicit feedback for adaptations to the intervention.

**Implementation** is defined as 1) the intervention agents’ adherence to the CASP schedule of session delivery (1, 2-, 4-, 7-
and 11-weeks contact points), 2) the impact of the CASP training program and 3) the costs of the intervention. Timeliness of CASP sessions as delivered by CHOs will be measured via program data, specifically CHO records. Knowledge and skills improvement due to the CASP training will be measured by a pre-post knowledge and skills assessment with nurses and CHOs.

**Cost** will be assessed from the health system (costs required to run the program), patient (healthcare expenses, quality of life), and societal (e.g. productivity losses) perspectives with a sub-sample of participants from the main participant pool in both arms. The sub-sample will be selected using a simple random number generator, ensuring every participant in the main sample has an equal probability of inclusion and minimizing selection bias. If a participant has been selected as part of the cost sub-sample, the cost data will be collected along with the rest of the study data that is relevant at that timepoint.

The health system costs will be stratified based on the agencies incurring the cost and the nature of the cost (start-up capital cost and recurrent costs). The random sub-sample of participants in the intervention and control groups (n=100, 25 per district) will be asked about their
**medical costs and productivity losses** in the previous four weeks using a modified Treatment Inventory of Costs in Patients (TIC-P) (Hindi)
^
22
^ at baseline and at 6 months follow up.

The TiC-P is a reliable instrument for collecting data on healthcare utilization and productivity loss in patients with mental health problems.
^
22
^
**Quality of life** will be assessed using the Hindi EuroQol-5D-5L (EQ-5D-5L) at baseline and at 6 months follow up. The EQ-5D-5L is a quality-of-life measure which has been widely used in India.
^
23
^ It measures quality of life via five dimensions, namely mobility, self-care, usual activities, pain/discomfort and anxiety/depression. Each dimension is measured by a Likert scale containing five levels spanning from a no problem to an extreme problem level.

*Secondary outcome measures*
1.Suicidal behavior

A modified Hindi version of the Columbia Suicide Severity Rating Scale (C-SSRS) Modified Screener Version
^
24
^ will measure suicidal behavior (suicidal intention, ideation, planning and fatal and non-fatal suicide attempt) at baseline and 6-
and 12-
month follow up. The Modified C- SSRS Screener is a semi-structured tool which measures the risk of suicide by inquiring about suicidal behaviour in the person’s lifetime (baseline) and since the last contact point (follow up). The screener consists of 6 questions and can be completed in a few minutes. For the purposes of this study, a lifetime measure was added to the screener to collect data on previous history of suicide ideation and behaviour at baseline. Specifically, the tool explores:
1.The presence of thoughts about suicide (suicidal ideation),2.Actions taken by the individual, in relation to preparing for suicide,3.Instances when the person has either attempted suicide or initiated a suicide attempt that was interrupted by another person or halted voluntarily, and the timing of this (lifetime, since last contact).

The C-SSRS has been translated in over 60 countries (including Hindi, and in India) and takes approximately 5 minutes to complete when administered as a clinical interview. The scale can be used by non-specialists across a range of settings, including healthcare settings.
2.Symptoms of depression

The Hindi Patient Health Questionnaire (PHQ-9)
^
25
^ assessment can be used as a screening tool as well as measures of symptom severity for depression. The nine-item PHQ-9 uses a 4-
point Likert-scale with items ranging from 0 (not at all) to 3 (nearly every day). The PHQ-9 has been validated, widely used, and found to be suitable for use in India.
^
26
^

